### Study design

The study is an experimental trial with an untreated control group, adhering to the Consolidated Standards of Reporting Trials (CONSORT). The study will be conducted in three main phases: Phase I (problem identification and quantification), Phase II (intervention development and implementation) and Phase III (evaluation of intervention). The outcome of the study will be assessed twice, at baseline and post-intervention. The intervention will be tested on households, which will receive structured education on fruit and vegetable intake, as well as methods for waste and food preservation. Women in the household will be educated on food preservation methods and how to store various types of fruits and vegetables at home. They will receive intervention for 6 months.

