### Dietary diversity score

A 24-h dietary recall will be conducted to assess food intake. Participants will report all food and beverages consumed in the 24 h before the interview (41). Foods will be classified under ten categories based on FAO dietary diversity guidelines (30, 31):

Roots and tubersCereals and grainsNuts and seedsMeat, poultry, and fishEggsDairyDark leafy vegetablesVitamin A-rich fruitsOther fruitsOther vegetables

Minimum dietary diversity will be defined as consumption of at least five out of ten food groups for women, and four out of seven for children, per WHO/FAO guidelines (9, 32). If a food group is consumed, a score of 1 will be given; otherwise, a score of 0.

A fruit and vegetable frequency questionnaire will also be used to assess the frequency of consumption of different fruits and vegetables. This structured questionnaire will be interviewer-administered and developed based on locally available produce. Women will report the frequency of fruit and vegetable consumption as: more than once daily, once a week but not daily, once a month but not weekly, or rarely/never. The same approach will be used for their children.

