### Intervention design and strategy

This study will implement a structured, community-based nutrition education and counselling program targeting women and children in the intervention communities of Kpedze and Amedzofe. In contrast, Abutia Kissiflui and Dededo will serve as control communities, with no intervention exposure. Such community-level strategies have been shown to improve food handling practices and reduce household-level losses in African settings (15). The aim is to enhance knowledge and practical skills on fruit and vegetable storage, reduce household-level post-harvest losses, and improve dietary practices.

The intervention will span a six-month period and will be coordinated by a trained dietitian, supported by three community health nurses. Educational meetings will occur monthly, and additional counselling will be provided through bi-weekly home visits and telephone interactions. Educational materials such as visual posters, handouts, and illustrative charts will be developed in local languages to ensure cultural relevance and ease of understanding. Group sessions will be interactive, allowing participants to ask questions and share experiences. Each session will last approximately 45 min and accommodate 5–10 women per group (Table 1).

**Table 1 tab1:** Lesson plan for nutrition education.

Month	Topic	Content	Rationale and literature support
Month 1	Importance of Fruits & Vegetables on Nutritional Status	Benefits, local examples, myths and facts	Dietary diversity and intake of micronutrient-rich foods like fruits and vegetables are critical for preventing undernutrition and anaemia in women and children (14). Awareness helps reshape food choices.
Month 2	Fruits and Vegetables Waste and Its Implications	Drivers, causes, prevention	Community-level losses reduce availability of key nutrients. Kitinoja and Kader (6) and Sheahan and Barrett (19) show that household knowledge on proper handling can reduce loss and improve food security.
Month 3–4	Fruit and Vegetable Preservation and Storage	Low-cost storage methods (e.g., clay pot coolers, FIFO), meal planning	Ambuko et al. (3) and Stathers and Mvumi (36) support the use of low-cost post-harvest technologies in rural African communities. FIFO principles help manage perishables better.

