### Secondary outcome

The secondary outcomes will be to evaluate the fruit and vegetable intake of women and children, post-harvest practices among farmers, traders, and women, food waste behaviour of women, BMI-for-age in women and children, the knowledge level of women regarding fruits and vegetables, and the impact of these on nutritional outcomes (Table 2).

**Table 2 tab2:** Table of primary and secondary outcomes.

Outcome type	Outcome	Measurement method	Assessment time points
Primary	Anaemia status in women and children	Haemoglobin testing (Hemocue 501 meter)	Baseline and post-intervention
Primary	Dietary Diversity Score (DDS)	24-h dietary recall and food group classification	Baseline and post-intervention
Secondary	Household food waste behaviour	Structured food waste behaviour questionnaire	Baseline and post-intervention
Secondary	Fruit and vegetable intake	Food Frequency Questionnaire (FFQ)	Baseline and post-intervention
Primary	Post-harvest handling knowledge/practices	Survey and Focus Group Discussion	Baseline
Primary	Anthropometric measurements (BMI, z-scores)	Height, weight using WHO protocol	Baseline and post-intervention

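### The fruit and vegetable frequency scale, as printed, has no answer for eating an item exactly once a day, so the secondary outcome of fruit and vegetable intake can be misclassified in women and children.

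*Protocol article*

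**What the plan says.** The questionnaire is described in the Dietary diversity score section of the protocol article. It is administered by an interviewer, built on locally available produce, and meant to "assess the frequency of consumption of different fruits and vegetables". The answers offered to women are "more than once daily, once a week but not daily, once a month but not weekly, or rarely/never". For the second population the section adds: "The same approach will be used for their children".

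Table 2, under Secondary outcome, lists fruit and vegetable intake as a secondary outcome, measured by this questionnaire at baseline and post-intervention. The Study objectives include the effect of the intervention on fruit and vegetable consumption, and the Study design section says that households receive "structured education on fruit and vegetable intake".

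Two other instruments touch on the same behaviour. For the 24-hour recall, "Participants will report all food and beverages consumed in the 24 h before the interview", and each food group then scores 0 or 1. The Food consumption score uses a 7-day recall in which fruits and vegetables are two of the weighted groups. Table 2 names neither as the measure of fruit and vegetable intake.

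**The concern.** A set of response options should give every respondent exactly one place. This one leaves a hole between its first and second options, and the hole lies at an ordinary eating frequency. Whoever falls into it must be moved up, moved down or left blank, and the article states no rule.

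The hole lies on the path along which intake would rise if the education worked. Someone who moves from a few times a week to once a day has improved, but the instrument named for this outcome cannot show it faithfully. What appears depends on an unstated coding habit, which may also differ between baseline and endline. An analysis plan cannot recover an answer that the form never offered.

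**Working it through.** The plan gives no figure to reproduce. The check has two steps.

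**Step 1: map each frequency to the printed options.** The nested reading takes the weekly and monthly options as at least once a week and at least once a month. The literal reading takes them as exactly once.

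| True frequency | Nested reading | Literal reading |
|---|---|---|
| Two or more times a day | Option 1 | Option 1 |
| Exactly once a day | none | none |
| 2 to 6 times a week | Option 2 | none |
| Once a week | Option 2 | Option 2 |
| 2 to 3 times a month | Option 3 | none |
| Once a month | Option 3 | Option 3 |
| Less than monthly | Option 4 | Option 4 |

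Once a day has no place on either reading. The other gaps appear only on the literal one. The nested reading is the natural one, because the exclusions attached to options 2 and 3 would be redundant if each meant exactly once.

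**Step 2: effect on an observed shift.** Let *s* be the true proportion moving from weekly to once-daily intake, and *c* the share of once-daily eaters coded up to option 1, with the rest coded down to option 2.

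- Apparent rise in option 1 = *c* × *s*.
- All coded down (*c* = 0): 0. Half coded up (*c* = 0.5): *s*/2. All coded up (*c* = 1): *s*, but labelled as more than once daily.

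The documents give no distribution of frequencies, so any value of *s* is an assumption. Purely as illustration, *s* = 10 points would show as 0, 5 or 10 points, and *s* = 20 points as 0, 10 or 20.

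Drift between rounds works in the same way. If a proportion *p* eats an item once a day at both rounds and the share coded up goes from *c*₀ to *c*₁, option 1 changes by *p* × (*c*₁ − *c*₀) with no true change. Drift common to both arms cancels in the between-arm contrast of changes if *p* is the same in both. It does not cancel in a within-arm comparison, and the Statistical analysis section plans within-group as well as between-group comparisons.

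**A cut that survives.** Options 1 and 2 both lie at or above once a week on the nested reading. A once-daily eater coded into either is still counted as at least weekly, so that cut does not depend on *c*. It is not protected if such answers were left blank.

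**The case against.** The best defence is that this is a wording slip. The nested pattern of the other options suggests that the top one was meant as once or more a day, and the questionnaire itself is not shown. That may be so, but nothing in the text says it, and the text is what fixes the scale. It bears on which fix applies, not on whether one is needed.

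Four stronger readings are tempting, and the documents do not support them.

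- **That once-daily eating is the target of the education.** No section or lesson plan sets a frequency goal. The stated aim is general: "The aim is to enhance knowledge and practical skills on fruit and vegetable storage, reduce household-level post-harvest losses, and improve dietary practices".
- **That unblinded staff will code in favour of the intervention.** The Randomisation and allocation procedure section says that participants cannot be blinded but that those collecting outcome data will be. If that holds, miscoding should be largely unrelated to arm and mainly dilutes the contrast. Self-report by unblinded participants remains, but the gap does not cause it.
- **That 2 to 6 times a week has no option either.** On the natural nested reading it belongs in the second option.
- **That the trial cannot see such a shift at all.** The 24-hour and 7-day recalls capture some fruit and vegetable eating. They do not cure the gap, as neither is the named measure: one scores presence on a single day, and the other feeds a weighted total across all food groups.

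It is also fair to say that only a secondary outcome is affected, and that once-daily eating of one particular item may be uncommon. The documents do not allow that proportion to be estimated.

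**Conclusion.** The point holds in this form: as printed, the scale is not exhaustive, because exactly once a day has no option for women or children, and this scale measures a named secondary outcome at both time points. Depending on coding, a true shift from weekly to once-daily intake could show as anything from nothing to its full size. That range is logical and rests on no assumed prevalence; how many answers are affected is unknown.

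With blinded collectors, the expected harm is misclassification and dilution between arms, plus possible drift between rounds. The conclusion assumes that the form in the field carries the options as printed. No primary outcome in Table 2 is touched. The point is worth correcting because the error is plain on the page and the remedy is cheap.

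**What to change.** 1. **If the top option was meant as once or more a day**, correct the text and confirm that the forms used at both rounds carried that wording. Nothing else is then needed.
2. **If not, and endline is still open**, use exhaustive, mutually exclusive options in both arms: twice or more daily; once daily; at least weekly but not daily; at least monthly but not weekly; rarely or never. On the nested reading, four of these match the printed options one to one, and once daily can be collapsed up or down. Compare the arms on the full endline scale. For change from baseline use at least weekly versus less than weekly.
3. **If endline is finished**, state the coding rule used at each round, report any answers left blank for want of an option, and use the weekly cut.

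The Study status and timeline section has data collection running to 31 July 2025, and Version 1.0 is dated June 9, 2025, so either the second or the third case may apply.

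The change costs a small edit to one form, or only a change of cut. The real price is in the analysis. Change from baseline is limited to a coarser cut, which cannot show a move from weekly to daily intake. Under the second case that move can be seen only in the endline comparison, which has no like-for-like baseline on the full scale and only two communities per arm.

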### Food consumption score

The food consumption score (FCS) will be determined by asking participants to recall all food and beverage consumption in the 7 days before the interview. Food groups will include: main staples, pulses, meat/fish, fruits, vegetables, milk, oil, and sugar. Consumption frequencies will be summed within each group and multiplied by group-specific weights. The weighted scores will be summed to derive the total FCS. FCS categories will be:

0–21: poor21.5–35: borderline35: acceptable

A score below 35 will be interpreted as indicative of household food insecurity.

### Household hunger scale

The Household Hunger Scale (45) will be used to assess food deprivation. This 3-question tool uses a 4-point Likert scale: 0 = never, 1 = rarely, 2 = sometimes, and 3 = often (more than 10 times in the past 30 days). The questions will assess:

Lack of food in the home due to lack of resourcesGoing to bed hungryGoing an entire day and night without food

### Haemoglobin testing

Capillary blood samples will be collected in the early morning (approx. 30°C, 80% humidity) using Hemocue® safety lancets. Procedures will follow WHO (33, 43) and Hemocue Hb 501 operating guidelines. Hands will be warmed and cleaned with 70% isopropyl alcohol. The third drop of blood (after discarding the first two) will be used to fill a microcuvette (~10 μL) for haemoglobin assessment using the Hemocue Hb 501 device. Samples will be taken from both women and children. Cuvettes not properly filled or with air bubbles will be discarded. Machines will be cleaned daily and validated using Hemotrol Level 1, 2, and 3 controls (Eurotrol E. V., Netherlands) (37, 38).

### Food waste behaviour

A structured questionnaire will assess food waste behaviour using adapted constructs from WRAP (34) and Stancu et al. (35). Variables will include:

Self-reported fruit and vegetable wasteIntention to reduce wasteAttitudes (financial, personal, health)Storage and planning habitsHousehold food preparation routines

Responses will be captured on a 7-point Likert scale. Mean construct scores will be used for further analysis.

### Body mass index (BMI)

The BMI-for-age z-score will be calculated using WHO Anthro Plus. BMI for women will be computed using WHO AnthroPlus by providing the weight and height in the software to provide the corresponding BMI (9).

### Theoretical framework

This study is designed as a pragmatic, theory-informed approach, based on principles from both the Health Belief Model (HBM) and Social Cognitive Theory (SCT) to influence individual and household food handling and nutrition-related behaviours. From HBM, the intervention addresses perceived susceptibility (e.g., risk of anaemia and malnutrition), perceived benefits (nutritional gains from reduced waste and improved diets), and self-efficacy (empowering women with practical storage and planning skills). From SCT, it leverages observational learning, reinforcement through group sessions, and environmental restructuring (e.g., improving storage practices) to promote sustained behaviour change. The design and messaging of the educational sessions were informed by prior empirical evidence in Sub-Saharan Africa showing that participatory and community-tailored education can effectively shift household nutrition and food waste behaviours (36).

### Intervention design and strategy

This study will implement a structured, community-based nutrition education and counselling program targeting women and children in the intervention communities of Kpedze and Amedzofe. In contrast, Abutia Kissiflui and Dededo will serve as control communities, with no intervention exposure. Such community-level strategies have been shown to improve food handling practices and reduce household-level losses in African settings (15). The aim is to enhance knowledge and practical skills on fruit and vegetable storage, reduce household-level post-harvest losses, and improve dietary practices.

The intervention will span a six-month period and will be coordinated by a trained dietitian, supported by three community health nurses. Educational meetings will occur monthly, and additional counselling will be provided through bi-weekly home visits and telephone interactions. Educational materials such as visual posters, handouts, and illustrative charts will be developed in local languages to ensure cultural relevance and ease of understanding. Group sessions will be interactive, allowing participants to ask questions and share experiences. Each session will last approximately 45 min and accommodate 5–10 women per group (Table 1).

**Table 1 tab1:** Lesson plan for nutrition education.

Month	Topic	Content	Rationale and literature support
Month 1	Importance of Fruits & Vegetables on Nutritional Status	Benefits, local examples, myths and facts	Dietary diversity and intake of micronutrient-rich foods like fruits and vegetables are critical for preventing undernutrition and anaemia in women and children (14). Awareness helps reshape food choices.
Month 2	Fruits and Vegetables Waste and Its Implications	Drivers, causes, prevention	Community-level losses reduce availability of key nutrients. Kitinoja and Kader (6) and Sheahan and Barrett (19) show that household knowledge on proper handling can reduce loss and improve food security.
Month 3–4	Fruit and Vegetable Preservation and Storage	Low-cost storage methods (e.g., clay pot coolers, FIFO), meal planning	Ambuko et al. (3) and Stathers and Mvumi (36) support the use of low-cost post-harvest technologies in rural African communities. FIFO principles help manage perishables better.
Month 5	Family Meal Planning & Use of Leftovers	Balancing meals, affordability, using local produce	FAO (1) showed that practical household-level meal planning improves intake consistency and reduces waste, especially among low-income households.
Month 6	Review	Reinforce key lessons, feedback from participants	Participatory reinforcement models improve retention and empower learners (Kumar et al., 2020). This month strengthens the learning cycle and evaluates uptake.

### Procedure for nutrition counselling session

Counselling sessions will be conducted privately, either in community meeting spaces or during home visits. Each session, lasting up to 30 min, will be delivered in a participant’s preferred language to ensure comprehension.

The key steps will include:

Obtaining written or thumbprint consent from participants.Conducting a brief dietary assessment.Providing tailored guidance on post-harvest handling, appropriate storage methods, and reducing waste.Distributing a simple dietary guide/manual developed for the study.Following up with progress reviews every two to three weeks via calls and home visits.

## Outcomes

### Primary outcome

The primary outcome is to assess the impact of post-harvest loss of fruits and vegetables on the nutritional status of women and children.

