## Study objectives

The primary objective of this study is to investigate the relationship between post-harvest losses of fruits and vegetables and the nutritional status of women and children in the Ho West District of Ghana. Specifically, the study aims to estimate the extent and drivers of post-harvest losses at the farm, retail, and household levels, to determine the nutrient losses associated with post-harvest waste of fruits and vegetables, to examine the relationship between the nutritional status of women and children in households and fruits and vegetables losses and to evaluate the effect of a structured community-based nutrition education and counselling intervention on post-harvest practices, fruit and vegetable consumption, and nutritional outcomes.

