### Statistical analysis

Statistical package for social sciences (SPSS) (IBM Corp. Released 2022. IBM SPSS Statistics for Windows, Version 30.0. Armonk, NY: IBM Corp) will be used for the data analysis. The Kolmogorov-Smirnov and Shapiro-Wilk tests will be used to assess the normality of the quantitative data. A *p*-value less than 0.05 indicates that the data is not normally distributed, and vice versa. The characteristics of the study participants will be analysed using descriptive statistics. A chi-square test will be done to assess the relationship between categorical variables. Fisher’s exact test will be employed to determine the significance level. Parametric tests will be used to analyse normally distributed data, and non-parametric tests will be used to analyse data that is not normally distributed. Parametric tests will be presented in terms of mean and standard deviation, and non-parametric tests will be presented in terms of median (maximum-minimum). A t-test will be conducted to compare the mean differences of the outcomes of interest within and between study groups at baseline and post-intervention. Regression analysis will be conducted to predict the drivers of fruit and vegetable loss, adjusting for age and gender. Partial correlation will be used to assess the strength of association among the variables. All *p*-values will be significant at *p* < 0.05.

The primary analysis will follow the intention-to-treat (ITT) principle, including all participants as initially allocated, regardless of their adherence to the intervention protocol. This approach ensures an unbiased estimate of the intervention effect. For secondary per-protocol analyses, only participants who fully adhered to the intervention will be considered. To address missing data, particularly in outcome measures such as dietary assessments and anthropometry, multiple imputation methods will be employed under the assumption that data are missing at random. Sensitivity analyses will be conducted to assess the robustness of results. This strategy helps maintain the validity and reliability of findings despite potential data gaps.

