## Summary

The current study is grounded in the urgent need to address the dual challenges of post-harvest loss (PHL) and malnutrition, particularly in vulnerable populations such as women and children in rural Ghana. While PHL has been widely acknowledged for its economic challenges, its direct nutritional consequences remain inadequately explored in both scientific literature and policy discourse. This study was designed to respond to this gap by systematically examining how losses of nutrient-rich perishable foods, fruits and vegetables, along the value chain, compromise food availability, accessibility, and ultimately the nutritional status of women and children. This rationale is firmly rooted in the under-recognised link between food systems inefficiencies and public health outcomes.

The study offers three significant contributions. First, it aims to provide rigorous scientific evidence on the extent and drivers of PHL and their association with dietary diversity, food consumption scores, household hunger levels, haemoglobin concentrations, and anthropometric outcomes. Second, it introduces an integrated, community-based educational intervention aimed at improving knowledge and practices regarding post-harvest handling and consumption of fruits and vegetables. Third, the study contributes to policy development by generating context-specific, evidence-based recommendations for local and national decision-makers, agricultural stakeholders, and public health practitioners. These recommendations will support more resilient and nutrition-sensitive food systems.

The findings are expected to influence practice through the development of scalable educational models and post-harvest management strategies. On a policy level, results will provide an empirical basis for aligning agricultural and nutrition policies, especially in contexts where food loss directly undermines nutrition outcomes. The study also fills a crucial knowledge gap by demonstrating the direct link between food loss and micronutrient deficiency risks among women and children. Ultimately, this research supports the broader global agenda of sustainable food systems transformation, offering an interdisciplinary approach that integrates agriculture, nutrition, and public health for improved outcomes.

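### The stated primary question is the impact of post-harvest loss on nutrition, but the primary intention-to-treat contrast estimates the effect of a bundled education package, so an arm difference cannot by itself be credited to reduced loss

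*Protocol article*

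**What the plan says.** Under Outcomes, Primary outcome, the article states: "The primary outcome is to assess the impact of post-harvest loss of fruits and vegetables on the nutritional status of women and children". Study objectives gives the same emphasis: "The primary objective of this study is to investigate the relationship between post-harvest losses of fruits and vegetables and the nutritional status". The last of the specific aims in that section is a different one: "to evaluate the effect of a structured community-based nutrition education and counselling intervention on post-harvest practices, fruit and vegetable consumption, and nutritional outcomes".

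The Statistical analysis section makes intention-to-treat by initial allocation the primary analysis and says of it: "This approach ensures an unbiased estimate of the intervention effect".

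Intervention design and strategy describes what is allocated. Its stated aim covers storage skills, lower household losses and better dietary practice. In Table 1, month 1 is "Importance of Fruits & Vegetables on Nutritional Status", months 2 to 4 cover waste, preservation and storage, and month 5 includes "Balancing meals, affordability, using local produce". The counselling procedure adds a brief dietary assessment and a dietary guide to tailored advice on handling, storage and waste. On the comparator: "Abutia Kissiflui and Dededo will serve as control communities, with no intervention exposure".

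The Summary says that the study fills a knowledge gap by "demonstrating the direct link between food loss and micronutrient deficiency risks among women and children".

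**The concern.** The primary question names loss as the cause and nutritional status as the effect. The primary analysis compares communities that were offered a package with communities that were not. These are different quantities, and the package contains elements that could change what women and children eat without any change in how much produce is lost.

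What is at stake is the conclusion. If dietary diversity or anaemia improves in the intervention arm, the primary outcome as worded invites the statement that less loss improved nutrition. The Summary says that the results will give an empirical basis for aligning agricultural and nutrition policy. A policy of investing in loss reduction and a policy of investing in nutrition education are different policies, and this contrast cannot tell them apart.

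**Working it through.** No arithmetic applies. The check is whether the stated question and the stated contrast concern the same quantity.

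**1. The question.** Primary outcome: exposure is post-harvest loss, response is nutritional status. The primary objective in Study objectives has the same pair, worded as a relationship.

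**2. The contrast.** Statistical analysis: all participants as allocated, giving the intervention effect. Exposure is the offer of the package, response is the outcome measured.

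**3. When the two would coincide.** Write Z for allocation, L for household loss, D for dietary choice that does not depend on loss, and Y for a nutritional outcome. In the simplest additive picture:

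effect of Z on Y = (part through L) + (part through D)

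The intention-to-treat difference estimates the left-hand side. It can be read as evidence about L only if the part through D is zero, that is, if the package can affect nutrition solely by reducing loss.

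**4. Whether the documents support that condition.** They point the other way:

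- The stated aim of the intervention includes better dietary practice alongside storage and loss reduction.
- Month 1 in Table 1 is about the nutritional value of fruit and vegetables, and its rationale is that awareness changes food choices. That route needs no change in loss.
- Month 5 covers balanced and affordable meals. Months 3 and 4 list meal planning together with storage methods.
- Counselling includes a dietary assessment and a dietary guide.
- The control communities receive none of this, and no arm receives storage teaching alone or diet teaching alone.
- Dietary Diversity Score, marked primary in Table 2, is an outcome that diet teaching plausibly moves.

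**5. Whether another planned analysis answers the loss question.** The regression described has fruit and vegetable loss as its outcome, with drivers as predictors. Partial correlation is planned among variables that the article does not name. It could describe how loss and nutritional status go together, but it is observational and supports a statement of association, not of impact.

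**6. What the article says elsewhere about attribution.** Concomitant care and permitted interventions attributes the measured effects to loss reduction and nutrition education jointly. That is the correct reading of the contrast, and it conflicts with a primary outcome that names loss alone.

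**The case against.** The strongest reply is that the article already separates the two questions. Study objectives lists the loss–nutrition relation and the intervention effect as distinct aims, the abstract calls the first an association, and the design puts problem quantification and evaluation of the intervention in different phases. Nowhere does the article say outright that the arm difference will be credited to reduced loss. The direct-link phrase is summary prose, and the Summary elsewhere speaks of association. A bundled package against an untreated control is also an accepted pragmatic design.

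Most of this stands. The design is sound for the aim on the education package, and no new arm is needed. But the separation does not cure the mismatch: both Study objectives and Primary outcome rank the loss question first, while the analysis called primary answers the other one.

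The reply is also right about the counselling. The tailored guidance listed there concerns handling, storage and waste; the diet elements are the assessment and the guide. The diet content is real but should not be exaggerated.

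Two stronger readings are tempting and are not supported:

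- **A numerical share.** A reader might count lesson months and infer what fraction of the effect is misattributed. Months 3 and 4 mix storage with meal planning, the rationale for month 5 includes waste reduction, and home visits and calls fall outside the count. The 30% in Sample size calculation covers nutrition and waste together, with no endpoint or scale, so it cannot be apportioned.
- **A confirmatory check.** A reader might infer that improved household food waste behaviour would show that the effect ran through loss. That questionnaire mixes self-reported waste with intentions, attitudes and routines that the package targets directly. It could improve while diet teaching produced all of the nutritional change.

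**Conclusion.** The concern holds as a mismatch between the stated primary question and the primary contrast. The intention-to-treat comparison concerns the effect of the whole education and counselling package against no intervention. It does not by itself estimate the impact of post-harvest loss, and it does not support the claim of a demonstrated direct link in the Summary.

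No size can be given: the documents contain nothing from which to divide an effect between the diet and loss pathways. The conclusion rests on one premise, that the diet content could affect at least some nutritional outcomes without changing loss. That is plausible and matches the article's own rationale for month 1, but it is not proven.

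A reader might go further and infer that the bundled design makes the trial uninformative. The documents do not support that: this mismatch does not prevent the contrast from addressing the package effect. The point limits what may be concluded and is worth correcting before results are reported.

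**What to change.** 1. **Primary outcome.** Reword so that the primary intention-to-treat question is the effect of the whole education and counselling package, compared with no intervention, on the nutritional outcomes in Table 2 (anaemia status, Dietary Diversity Score, anthropometric measurements).
2. **Study objectives.** Keep the loss–nutrition relation, which is already a separate aim, but label it an observational association that the arm contrast does not answer. Tie the primary analysis to the aim on the education package.
3. **Summary.** Replace the claim of demonstrating a direct link with wording about examining an association, and keep the joint attribution already given under Concomitant care and permitted interventions.

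No arm, measurement or visit changes. The article reports that no results had been analysed at submission, and its Protocol amendments section gives the route for documenting the change and notifying the ethics committee and the registry. The downside is a narrower headline: an effect of an education package, plus an association between loss and nutrition, in place of a causal statement about loss.
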